### Blinding

Blinding therapists or participants is not possible for the intervention under study. Assessors at baseline and follow-ups will be blind to the intervention arm. Participants will be reminded of the importance of assessors remaining blind to allocation as recommended,^34^ and assessors will report any instances of potential unblinding. The trial statistician will remain blinded to group allocation during analysis. It will not be possible to blind the qualitative analyst(s). It is not possible to blind YP, which could lead to reporting bias. We will mitigate this by using an interviewer-led criterion-based clinical interview to define the primary outcome and standardised prompts for questionnaires. We will also evaluate the consistency of effects for outcomes reported by different raters (YP and parents/carers).

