### Trial design

This is a multisite, two-arm, parallel-group effectiveness RCT with assessors blinded to allocation. YP will be randomised 1:1 to the intervention condition (the SWELL programme plus usual care) or the usual care only condition. Given that most YP do not receive preventive interventions, usual care is the appropriate comparator. The method of randomisation will be simple-permuted-block randomisation stratified by site, with the unit of randomisation being the YP (online supplemental material 2).

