#### SWELL programme

YP in the SWELL intervention arm will be assigned to an online group including 6–8 YP and a therapist. The group will meet via videocall for 60 min. Table 1 outlines the sessions which target factors hypothesised to contribute to the development/maintenance of depression. These include training in cognitive-restructuring skills and techniques for modifying cognitive, problem-solving, behavioural activation, assertiveness and relaxation. Continuation sessions involve revising and consolidating learning, planning how skills could be used in response to future stressors and troubleshooting attempts to apply skills. YP are provided with a workbook to help them follow the intervention content and apply the skills. Two parent information sessions are offered.

**Table 1 T1:** Overview of Skills for adolescent WELLbeing (SWELL)

Acute session 1	'Beginnings’Psychoeducation about stress and depression, identifying personal goals and measuring your mood.	Intervention components common to each sessionSession start: Ice breaker. Home practice review (excluding session 1). Mood check-in with prompts to consider contributory internal and external factors. Session end: Participants encouraged to share positive events that occurred during the previous week. Participants were encouraged to reflect on aspects of the session they found most helpful and to provide feedback on what could be different. Home practice is set related to applying learning from the content of the session in their day-to-day lives.
Acute session 2	'Coping with stress’Identifying negative automatic thoughts and triggering events.	
Acute session 3	‘Increasing positive and balanced thinking’Increasing positive and balanced thinking, review of personal goals.	
Acute session 4	‘Examining negative thoughts and sources of beliefs’Identifying unrealistic thoughts and underlying beliefs, changing these to more realistic thoughts.	
Acute session 5	'Problem solving’Problem solving – thinking of solutions, evaluating solutions, trying out solutions and evaluating their effects.	
Acute session 6	‘Being Assertive’Assertiveness training, communication styles.	
Acute session 7	'Behavioural activation’Behavioural activation and integrating into daily life (plans for action and developing positive habits).	
Acute session 8	Relaxation and ending the weekly MeetingsRelaxation techniques, progressive relaxation, pleasant imagery, breathing exercises.	

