### Analyses

The flow of participants through the trial will be presented as a Consolidated Standards of Reporting Trials diagram. Baseline demographic data will be presented for all consented and randomised participants, and patterns of attrition will be examined.

The primary analysis will be time-to-event analysis of the primary outcome (time to the first depressive episode collected at 9-month follow-up) and will use the complete case dataset. However, multiple imputation will be considered as a sensitivity analysis to examine possible dropout bias in the treatment effect estimate. Consistent with clinical practice, depression in the YP will be defined as YP depression reported by either parent/YP with a planned sensitivity check for YP report only. A Cox regression model will be used to determine the difference between trial arms, the HR and 95% CI. We will investigate whether a random effect to account for the group delivery clustering in the intervention arm needs to be included in the primary model. If the effect of the clustering is negligible, this will be excluded. Assumptions of the model (eg, constant hazard) will be checked to ensure model validity. Prespecified subgroups to be compared descriptively include those defined by baseline characteristics of the YP (eg, comorbidity) and parents (eg, depression status at randomisation). External treatment use will also be compared descriptively across study arms, and its effect will be evaluated by including this as a time-varying covariate in the Cox model.

Possible effect modification (eg, by PTO response, baseline demographic factors) will be investigated by including an arm*modifier interaction term. Mediation analyses will examine the effects of potential mediators (eg, improved problem-solving skills, improved parent-child relationship) on the primary outcome via inclusion of the mediator predictor in the primary model.

A sensitivity check will explore the effect of changes to inclusion criteria on the effectiveness of the intervention (online supplemental material 4). Only 20 participants were consented prior to the implementation of these changes, meaning their inclusion is unlikely to influence the main study findings in a substantial way.

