Repeated measures analysis will be used for secondary outcomes collected at 3 months and 9 months. Linear mixed effects regression will be used to account for clustering by group delivery in the intervention arm (partial effect model) and will include baseline values as covariates where appropriate. Where the assumptions of the linear regression model are not met, transformation or categorisation will be considered. Logistic regression models will be used for binary outcomes. Main group effects and 95% CIs will be presented for all outcomes.

Qualitative data analysis will use a thematic analysis approach, a process of identifying, analysing, reporting and interpreting patterns or themes.^48^ Codes will be applied to broad themes and transcripts will be examined to identify key themes and subthemes. To ensure validity, a proportion of transcripts (approximately 20%) will be double-coded by a second qualitative researcher, and any discrepancies resolved by discussion. Thematic analysis will be supported by NVivo software.

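### The statistician cannot stay blinded throughout the analysis, because the clustered models need a SWELL group identifier that only intervention participants have

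*Protocol article*

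**What the plan says.** On the statistician, the Blinding section says: "The trial statistician will remain blinded to group allocation during analysis". It gives no exception and no point at which the blind ends. The same section concedes that the qualitative analysts cannot be blinded.

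The Analyses section describes two uses of the therapy group as a cluster:

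- **Primary outcome:** the sentence on the random effect begins "We will investigate whether a random effect to account for the group delivery clustering in the intervention arm needs to be included in the primary", where the last word refers to the Cox regression. The rule that follows is: "If the effect of the clustering is negligible, this will be excluded". The article gives no threshold for negligible.
- **Secondary outcomes:** "Linear mixed effects regression will be used to account for clustering by group delivery in the intervention arm (partial effect model"). This is a commitment, not an option.

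Two further choices are left open. For secondary outcomes: "Where the assumptions of the linear regression model are not met, transformation or categorisation will be considered". For the primary outcome: "multiple imputation will be considered as a sensitivity analysis to examine possible dropout bias in the treatment effect estimate".

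Therapy groups exist in one arm only. The SWELL programme section says: "YP in the SWELL intervention arm will be assigned to an online group including 6–8 YP and a therapist". The Trial design section contrasts "the intervention condition (the SWELL programme plus usual care) or the usual care only condition".

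**The concern.** A partially clustered model needs to know which group each participant belonged to. Here, belonging to a group is the same as having been allocated to SWELL. Labelling the arms A and B hides nothing once the group variable is in the file, because the arm with groups is the intervention.

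Two things are at stake. The first is accuracy: a trial report that repeats the Blinding sentence would describe as blinded some analyses that were not. The second is room for discretion. The plan decides from the data whether to keep the cluster term in the primary model. Keeping or dropping it can change the standard error and the confidence interval of the primary treatment effect. As described, whoever makes that decision has the means to see which arm is which.

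**Working it through.** The plan gives no figure to reproduce on this point. The check compares the sections and adds a short count.

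**Inputs**

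- Sample size 400 (Sample size section), allocated 1:1 (Trial design section): 400 / 2 = 200 per arm.
- 6 to 8 young people per SWELL group (SWELL programme section); no groups in usual care (Trial design section).

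**Number of group identifiers**

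- Groups of 8: 200 / 8 = 25 groups.
- Groups of 6: 200 / 6 = 33.3, so about 33 groups.
- Usual care: 0 groups.

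**Does the identifier reveal the arm?** A mock file of 400 participants was built, with 200 per arm and the intervention arm split into groups of 7 (the last group smaller). Two ways of coding the controls were tried:

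- Controls have a missing identifier. The rule that anyone with an identifier is SWELL classified 100% correctly.
- Controls are coded as single-person clusters. The rule that anyone in a cluster larger than one is SWELL classified 100% correctly.

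**Which planned steps need the identifier?**

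| Step | Group identifier needed? | Can be blind under coded arms? |
|---|---|---|
| Writing the SAP, data checks | No | Yes |
| Cox model without a cluster term | No | Yes |
| Checking whether the Cox model needs the random effect | Yes | Not as described |
| Cox model with the random effect | Yes | Not as described |
| Mixed models for secondary outcomes | Yes | Not as described |
| Choosing a transformation or categorisation; deciding on imputation | No | Yes, if settled before the identifier is merged |

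The contradiction is therefore confined to the clustered models and the decision about the cluster term. That decision cannot be moved to a blinded stage by looking at pooled data, because clustering by group cannot be assessed without knowing the groups. It can only be prespecified.

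**The case against.** The strongest reply has four parts.

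**The primary model can be fitted blind.** This is right for the unclustered Cox model. A reader might infer that no part of the analysis can be blinded, or that the primary model cannot be fitted under the stated blind. The article does not support that, since the random effect in the primary model is conditional. The check that decides on it still needs the identifier.

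**The blind could be preserved.** Controls could be given pseudo-groups of similar size with a separate cluster variance in each coded arm, or a second statistician could run prespecified code. Either could work, fully or largely. Neither appears in the article, and either would be a change to the plan as written.

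**The full protocol or the SAP may settle who holds the identifiers.** It may. Missing detail of that kind is not the point here. The point is that an unqualified statement conflicts with models described in the same article. If another person is to fit the clustered models, the sentence should say so.

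**The consequences are limited.** This stands in large part:

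- Outcome assessors are blinded and the primary outcome comes from a criterion-based interview, so ascertainment is not affected.
- The primary dataset is fixed as complete case, and imputation is only a possible sensitivity analysis. Transformation concerns secondary outcomes only.
- The rule for combining parent and young person reports is already fixed, so it is not an open choice.
- A reader might take the blind to be the declared safeguard for model choices. The article does not say so; that is its usual purpose, not a stated one.
- A reader might add that attendance records and intervention experience questionnaires also reveal the arm. None of the described outcome models requires them and nothing places them in the analysis file, so the argument should not rest on them.

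**Conclusion.** The point holds in a limited form. As described, the statistician cannot remain blinded while fitting the secondary mixed models or while deciding whether the primary Cox model keeps its cluster term. Once the identifier is merged, allocation can be read for all 400 participants: about 200 in some 25 to 33 groups, and about 200 in none. Steps that do not use the identifier can still be blind.

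For the primary result, the exposed choice is the cluster term. Its effect on the confidence interval cannot be sized from the article, which gives no intracluster correlation. No bias in a particular direction is shown, and no error rate or power figure changes.

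The conclusion assumes that one trial statistician fits all the models described and that controls are not given artificial groups. The article mentions no other arrangement. This should be corrected, but it does not threaten the validity of the trial.

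**What to change.** Reword the sentence in the Blinding section, and carry the same wording into the SAP and the trial report. The statistician is blinded until the SAP and analysis code are signed off and the database is locked; the clustered analyses are then run with allocation identifiable, because the group variable reveals the arm.

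Before the group identifiers are released:

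1. Prespecify the cluster term in the primary model instead of deciding it from the data. Always retaining it is one option and removes the need for a threshold for negligible.
2. Fix the rules for transforming or categorising secondary outcomes, using pooled data without arm or group.
3. Fix whether and how the imputation sensitivity analysis will be done, on the same basis.

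Do not describe the clustered analyses as blinded. If the team prefers to keep the blind, a separate statistician could fit the clustered models from signed-off code, and the sentence should then say so.

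The cost is small: a change of wording, holding back the group identifier file until sign-off, and giving up the claim of a fully blinded analysis.

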### Interventions

#### Parent treatment optimisation

The rationale of PTO is to provide good quality healthcare with the aim of improving the effect size observed previously for the YP intervention.^16^ Parents meeting the threshold for depression at screening (defined as a Patient Health Questionnaire-9^35^ score≥10) will be offered up to 12 weeks of PTO. We expect 40% of parents to meet this criterion.^16 30^
Box 2 lists PTO components based on evidence-based practice.^31^ In brief, an initial assessment by a psychiatrist with recommendations to optimise depression treatment including psychoeducation, referral to online guided CBT and medication review (box 2). Fortnightly check-ins by a psychiatrist/psychology assistant will monitor progress. The duration of PTO was based on adult depression treatment trials where most individuals who remit/respond do so within 10–12 weeks^36^,^38^ and to allow the intervention for YP (delivered after PTO) to be delivered within projected timelines. The treatment team includes consultant trial psychiatrists ([name], [name]) at Cardiff University Psychiatry Service (CUPS) and psychology assistants. A team member will contact parents who screen positive for depression to arrange appointments (in person at the CUPS clinic or video/phone call; usually via videocall) and the parent’s GP will be informed.

Box 2Components involved in parent treatment optimisation
**Initial consultation**
Assessment: parent is assessed by the psychiatrist in a 1-hour consultation (approximately) conducted in person or via video/phone call.Psychoeducation: brief psychoeducation about depression and self-management advice (eg, activity scheduling, lifestyle approaches) will be delivered by the psychiatrist at the end of the initial consultation.Guided online cognitive behavioural therapy (CBT): psychiatrist signposts the parent to the 8-module ‘Space from Depression’ or ‘Space from Depression and Anxiety’ programmes on SilverCloud platform (https://pthb.nhs.wales/services/adult-and-older-peoples-mental-health-services/silvercloud-online-cbt/)^36 48^ or equivalent. They will be advised by the psychiatrist to complete one module (roughly 1 hour each in length) per week, as recommended.^49^ The SilverCloud online CBT package will be guided as this increases adherence and response for those with moderate depression.^28^Medication review: psychiatrist to review the parent’s medication history and make recommendations to the general practices (GP) regarding the medication and other aspects of the management as required.
**Follow-up consultations**
According to the needs of the individual as assessed by the psychiatrist, either the psychiatrist or a psychology assistant checks in with the parent once every 2 weeks in person or via video or phone call to check on their progress for up to 12 weeks. Ahead of each check-in, a reminder will be sent (eg, via text or email) to the parents with a link to complete a Patient Health Questionnaire-9 (PHQ-9)^35^ questionnaire to assess their depressive symptoms.All parent treatment optimisation will involve assessment and signposting to guided internet-based CBT with regular follow-up. However, not all components or steps need to be completed for every parent and will be provided depending on the needs of the individual. The psychiatrists are highly trained and will use their clinical judgement regarding the treatment approaches. Therefore, there are no pre-specified escalation protocols, but typically the treatment would be escalated if there is no improvement in symptoms or if there is a deterioration in symptoms or clinical concern (eg, risk of self-harm or suicide).

#### SWELL programme

YP in the SWELL intervention arm will be assigned to an online group including 6–8 YP and a therapist. The group will meet via videocall for 60 min. Table 1 outlines the sessions which target factors hypothesised to contribute to the development/maintenance of depression. These include training in cognitive-restructuring skills and techniques for modifying cognitive, problem-solving, behavioural activation, assertiveness and relaxation. Continuation sessions involve revising and consolidating learning, planning how skills could be used in response to future stressors and troubleshooting attempts to apply skills. YP are provided with a workbook to help them follow the intervention content and apply the skills. Two parent information sessions are offered.

**Table 1 T1:** Overview of Skills for adolescent WELLbeing (SWELL)

Acute session 1	'Beginnings’Psychoeducation about stress and depression, identifying personal goals and measuring your mood.	Intervention components common to each sessionSession start: Ice breaker. Home practice review (excluding session 1). Mood check-in with prompts to consider contributory internal and external factors. Session end: Participants encouraged to share positive events that occurred during the previous week. Participants were encouraged to reflect on aspects of the session they found most helpful and to provide feedback on what could be different. Home practice is set related to applying learning from the content of the session in their day-to-day lives.
Acute session 2	'Coping with stress’Identifying negative automatic thoughts and triggering events.	
Acute session 3	‘Increasing positive and balanced thinking’Increasing positive and balanced thinking, review of personal goals.	
Acute session 4	‘Examining negative thoughts and sources of beliefs’Identifying unrealistic thoughts and underlying beliefs, changing these to more realistic thoughts.	
Acute session 5	'Problem solving’Problem solving – thinking of solutions, evaluating solutions, trying out solutions and evaluating their effects.	
Acute session 6	‘Being Assertive’Assertiveness training, communication styles.	
Acute session 7	'Behavioural activation’Behavioural activation and integrating into daily life (plans for action and developing positive habits).	
Acute session 8	Relaxation and ending the weekly MeetingsRelaxation techniques, progressive relaxation, pleasant imagery, breathing exercises.	
Parent information session 1	A 60-minute session during week 1 of the acute session phase. Includes details about the practicalities of the young person attending the group, theory underlying the intervention, how parents can support young people to engage with home practice activities between sessions and an overview of the content of each session. Focuses on the content of sessions 1–4.	
Parent information session 2	A 60-minute session during week 4 of the acute session phase. As above but focuses on the content of sessions 5-8 and the continuation sessions.	
Continuation session 1	Emergency planning, maintaining gains.	
Continuation session 2	Review of cognitive restructuring, introduce thought-stopping techniques.	
Continuation session 3	Review of behavioural/emotion-focused content (problem solving, behavioural activation, assertiveness training).	
Therapist training and ongoing quality assurance	Training in SWELL includes 5 days of structured teaching on the underlying theory and rationale and practical delivery of the intervention including training in non-specific psychotherapeutic skills (eg, active listening, Socratic questioning) and running therapeutic groups (eg, managing group dynamics). In addition, therapists will observe the delivery of the intervention by the clinical psychologist before being observed delivering it themselves. Therapists’ competency delivering SWELL will be assessed using an adapted version of the Assessment of Core CBT Skills (ACCS^50^). Therapists will require a rating of “Good” in all domains before being approved to deliver the intervention independently. On completion and sign-off of therapists to deliver the intervention independently, an early (session 1–4) and late (session 5–8) will be selected at random (using a random number generator) to be listened to and rated by the therapist, and independently rated by a clinical psychologist using the ACCS, with feedback provided during monthly individual supervision sessions with particular focus on areas rated as less than ‘Good’. In subsequent supervision sessions, close attention will be paid to areas rated less than ‘Good’ in a previous session to ensure therapists are able to rectify any issues. If ongoing issues are identified, further training will be provided.	

CBT, cognitive behavioural therapy.

